### Methodology

#### Data Collection

Study data are collected using paper case report forms. These paper documents will be kept in a locked cupboard accessible only to local research staff. Patient information is collected and stored by the investigators in a confidential REDCap (Research Electronic Data Capture system; Vanderbilt University), with password protection and restricted access. This will include patient information transcribed from the hospital’s electronic medical record. REDCap is a secure, web-based app designed for research studies, providing a validated data entry interface, audit trails for data tracking, automated export procedures, and secure procedures for data import [11]. Internet access to the REDCap database will use a secure server located at the University of Melbourne, Australia (REDCap consortium host). Access will be limited to local research staff, approved data administrators, and project statisticians.

All biological samples will be labeled with a reidentifiable study number. The electronic study information will be stored in a dedicated, limited-access clinical database. Only study investigators and key study staff will have access to the database. Biological samples will be stored at –80 °C until all samples are collected. They will then be processed in batches by the local pathology network according to standard protocols.

Epigenetic samples (buccal swabs) will be stored at –80 °C until all samples are collected. DNA will then be extracted using standard processes for DNA extraction, and samples will be prepared for shipping. Methylation analysis will occur at an external genomics facility [12,13]. Once processed, data will be interpreted with the assistance of appropriate clinicians at Murdoch Research Institute. These samples are hypothesis-generating only and will not be included in the prediction modeling.

#### Data Management

Management of comprehensive and valid records will be the responsibility of each site. To ensure a systematic approach to data collection, the same team of study nurses will work between the sites using the same protocol and standard operating procedures. Data integrity will be maintained through a review of the collected data prior to, during, and after each study visit. Medication and adverse event data will be reviewed during each study visit. In addition, every 3 months the study coordinator will review the data collected to ensure completeness and consistency of data. Any data discrepancies will be queried with the participant by email or telephone within 4 weeks of being noted. All data, including the attendance of study visits, will be captured on a REDCap database. This will ensure that the study can meet regular deadlines required for process reporting as required by the Human Research Ethics Committee.

#### Data and Safety Monitoring

We anticipate very few study-related adverse events or serious adverse events. The only anticipated adverse events are phlebotomy-related side effects (ie, bruising, bleeding, vasovagal syncope) and a negative psychological response to clinical visits (ie, having weight measured). These events will be circumvented by having provided participants with a full and comprehensive review of study visits at the time of enrolment and prior to each study visit.

Reports of measurements taken at the time of clinical visits including weight and bioimpedance data, and the results of laboratory tests that are clinically relevant, will be made available to participants. Results that are not clinically relevant will not be disclosed to participants as they will not impact clinical care and may be difficult to interpret (ie, lack of reference ranges in pregnant women). Any concerning results will immediately be relayed to the treating maternity team. All other results will be reviewed within 1 week. The outcomes of participants will be discussed with the chief investigator each month. Any systematic problems with data management and adverse event monitoring or reporting will be rectified. REDCap queries will be addressed monthly by the study coordinator and reviewed quarterly by the study statistician.

### Ethical Considerations

This is a prospective observational cohort study that intends to identify the metabolic disease risk factors, or combination of factors, that are most likely to cause adverse maternal and fetal health outcomes. No study-related adverse events are anticipated. The study has been granted ethics approval from the Royal Melbourne Hospital Human Research and Ethics Committee (HREC/90080/MH-2022) and recruitment is ongoing. Each participant will provide written informed consent before any study activities are undertaken and participants are free to withdraw consent at any time. Confidentiality will be maintained and only group data will be presented. Dissemination will be through peer-reviewed publications at national and international conferences, national and international obstetric medicine societies, and specialist colleges.

### Statistical Methods

This study will follow the Transparent Reporting of a Multivariable Prediction Model for Individual Prognosis or Diagnosis reporting guidelines for prognostic studies [14]. Summary characteristics of the study cohort will be described using means (with SD) or medians (with IQRs) for continuous variables, depending on the shape of the distribution, and numbers and percentages for categorical variables.

A risk calculator will be developed to determine the risk of an abnormally grown fetus (ie, the primary outcome of the study). Participant data will be split randomly into either training (70%) or validation (30%) datasets according to standard prediction model methods. Multivariable logistic regression analysis will be conducted to identify candidate predictors of poor pregnancy outcomes due to metabolic disease. After starting with the most comprehensive model that includes all potential risk factors for an LGA or SGA offspring (ie, the primary outcome). These include categorical variables including maternal SES (based on postcode), maternal parity, maternal smoking status, maternal obesity class, maternal preexisting diabetes, maternal preexisting renal disease, essential hypertension, use of antihypertensive medication, use of metformin, gestational hypertension, preeclampsia/eclampsia, previous LGA/SGA offspring, major congenital anomaly, and continuous variables including maternal age, maternal gestational weight gain, maternal glycemic control (HbA_1c_), total daily dose insulin, maternal systolic blood pressure, maternal diastolic blood pressure, birthweight of previous offspring, fasting glucose, plasma insulin, plasma C-peptide, plasma leptin, HOMA-IR.

A backward selection method will be performed to determine which combination of risk factors generates the most parsimonious predictive model. The number of candidate variables will be limited to data collected in the dataset. From this parsimonious model, model coefficients and the associated 95% CIs will be extracted to derive the risk score for predicting the delivery of LGA/SGA offspring. Internal validation of the model will be performed using 5-fold cross-validation and bootstrap validation. The performance of the model will be assessed using the AUC and calibration slope.

A similar approach will be taken for the secondary outcomes, and these models will be used to develop risk calculators for a composite of neonatal adverse outcomes and a composite of maternal adverse outcomes. Ongoing statistical input will be provided by the University of Melbourne.

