### Eligibility and Recruitment

#### Inclusion Criteria

Eligibility for the study will be women aged 18 years and older with pregnancies of 20±4 completed weeks of gestation who provide written consent and are attending a prespecified study site for maternity care. The study will include those with multifetal pregnancies, chronic disease, and those using medications of any type. Women from non–English speaking backgrounds will be included and telephone interpreting services and cultural liaison officers will be used as required.

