#### Medical History and Medications

At the first visit, a full medical history will be taken by a trained clinician including past medical history and surgical history. Outcomes of previous pregnancies will be recorded including outcome of the pregnancy, gestation, pregnancy complications, and (if relevant) birthweight and neonatal complications. Current medications including dose, and dosing schedule will be recorded. Smoking, alcohol, and recreational drug use will be recorded.

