### Why Existing Prediction Models Are Inadequate

There are very few studies that have aimed to predict adverse pregnancy outcomes based on the maternal phenotype, and most of these have used maternal characteristics in combination with obstetric tests such as biomarkers in blood or ultrasound [24-27]. To the investigator’s knowledge, there has only been one study that has used maternal prepregnancy characteristics to predict the risk of poor pregnancy outcomes [28].

The Generation R study group used easily obtainable maternal preconception characteristics including age, ethnicity, parity, BMI, and smoking status to model the risk of offspring born LGA/SGA. Basic models demonstrated an AUC of 0.63 (95% CI 0.61 to 0.65) and 0.64 (95% CI 0.62 to 0.66) for preterm birth/SGA and LGA, respectively. Interestingly, more complex models involving sociodemographic and dietary details only led to small improvements in the model [28].

However, the Generation R study was a population-based prospective cohort study that aimed to identify early and genetic causes and casual pathways leading to abnormal growth and development of the offspring [29]. Risk prediction modeling in this study focused on all potential causes of LGA and SGA in a whole population cohort. This study did not specifically focus on LGA/SGA in the context of metabolic disease, nor did it consider the metabolic outcomes of the mother. Women with metabolic disease are known to be at higher risk of adverse pregnancy outcomes than the general population [30]. This cohort requires information about the risk of poor pregnancy outcomes both for themselves and their offspring.

Within an established pregnancy, Frick et al [31] found that LGA offspring (>95th centile) could be predicted based on increasing maternal BMI, diabetes status, and the presence of chronic hypertension. However, this prediction was less accurate in non-Caucasian women, in smokers, and in nulliparous women. In parous women, LGA offspring were predicted based on the birth-weight Z-score of previous offspring, a prior history of GDM, and a decrease with interpregnancy interval. This study then refined the prediction model using early fetal ultrasonography [31].

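### Previous birthweight enters the full starting model as a plain continuous term, although women in a first pregnancy are eligible and have no value for it

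*Protocol article*

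**What the plan says.** The Statistical Methods section of the protocol article describes backward selection for the primary outcome, "starting with the most comprehensive model that includes all potential risk factors for an LGA or SGA offspring". The candidates are then named in two groups, categorical and continuous. The continuous group includes "maternal diastolic blood pressure, birthweight of previous offspring, fasting glucose". The categorical group includes "maternal SES (based on postcode), maternal parity, maternal smoking status" and, further on, "previous LGA/SGA offspring, major congenital anomaly". No interaction, nesting, separate model by parity or special coding is attached to the previous-birthweight term. The section adds that candidates are restricted to data that have been collected. It then applies a similar approach to the two secondary calculators.

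The Inclusion Criteria admit "women aged 18 years and older with pregnancies of 20±4 completed weeks of gestation", with no condition on earlier births. Medical History and Medications records details of earlier pregnancies, and qualifies one part of that record: "if relevant) birthweight and neonatal complications". The discussion of existing models reports that in a cited study, "In parous women, LGA offspring were predicted based on the birth-weight Z-score of previous offspring".

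**The concern.** A woman with no previous birth has no previous birthweight. The value does not exist, so this is not ordinary missing data, and imputation would estimate a quantity with no true value. A logistic model that holds the variable as a bare main effect can use only the rows where it is defined.

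Three things follow for the model as listed:

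- The full model is fitted to women with a previous birthweight only, and so is each selection step until this term is removed. Other candidates may be discarded on evidence from that subset alone.
- Within that subset parity has no nulliparous level, so two listed candidates cannot both do their work in the same fit.
- If the term survives selection, the resulting score has an input that a woman in her first pregnancy cannot supply. The Introduction and Conclusions present the calculator as a triage tool for any health care worker to use, with no restriction to women who have given birth before.

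The subset is also smaller than the cohort for which the sample size was justified.

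**Working it through.** **Inputs from the Sample Size section.** 500 recruited, 5% dropout, outcome in 20%, anticipated AUC 0.8, required minimum 440 women and 88 events, expected shrinkage of 10% or less (S = 0.90).

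**Input not in the document.** The share of the cohort with a previous birthweight. It is taken as an assumption over 40-70%. The outcome rate in that subset is assumed to be the same 20%.

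**Step 1: reproduce the plan's figures.** 500 × 0.95 = 475 women, and 475 × 0.20 = 95 events. For the minimum, AUC 0.8 and prevalence 20% under a binormal linear predictor give a Cox-Snell R² of 0.183 (maximum 0.632). The shrinkage criterion is N = P / [(S − 1) ln(1 − R²/S)]. The number of parameters P is not stated, so it was solved for. P = 10 gives 10 / [(−0.1) × ln(1 − 0.1827/0.9)] = 441, against the stated 440. At P = 10 the criterion on Nagelkerke R² needs 281 and the precision criterion 246, so shrinkage is the binding one. The plan's figure is reproduced.

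**Step 2: remove women with no previous birthweight.** Women = 475 × share; events = 95 × share. Expected shrinkage comes from solving the same formula for S at P = 10.

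| Assumed share with a previous birthweight | Women | Events | Expected S at P = 10 |
|---|---|---|---|
| 40% | 190 | 38 | 0.80 |
| 50% | 238 | 48 | 0.83 |
| 60% | 285 | 57 | 0.85 |
| 70% | 333 | 67 | 0.87 |
| Plan's target | 440 | 88 | 0.90 |

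**Step 3: find the break-even share.** 440 / 475 = 0.926. The stated minimum survives row deletion only if at least 92.6% of the analysed women have a previous birthweight. Equivalently, no more than 35 of the 475 could be in a first pregnancy or otherwise lack the value.

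**Step 4: look for a rule that prevents the deletion.** The sentence restricting candidates to collected data governs which variables are used, and previous birthweight is collected. It gives no rule for women to whom the variable does not apply. The categorical growth-history variable could carry a no-previous-birth level, but a continuous birthweight cannot. Nothing else in the article settles the point.

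**The case against.** The strongest reply is that this is a condensed candidate list in a journal article. It gives no coding for any variable and nowhere announces a complete-case analysis. A statistical analysis plan that is not shown could nest birthweight within parity, add a no-previous-birth category, or fit separate models by parity. Parity is listed as a candidate, the medical history qualifies the birthweight record, and the discussion ties the predictor to parous women. All three suggest that the investigators know it applies only conditionally.

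Much of this stands. The row deletion is what standard software does with the listed model; it is not a stated rule. A reader might infer that the plan intends to leave out first pregnancies, but the document does not support that, and listing parity points the other way. A reader might also infer that the calculator will necessarily give no valid risk for a first pregnancy. That holds only if the term survives selection. If it drops out, the final model can be refitted to all women, and the damage is limited to the steps taken before it left.

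Two further contrasts are tempting but are separate matters. One is the length of the candidate list against what the sample supports: by the formula above, all 475 women support only about 10.8 parameters. The other is the loss from the 70/30 split. Both would remain if every woman were retained.

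The reply does not remove the core point. The article goes beyond leaving coding open: it fixes the variable, its continuous form and its place in the full starting model. An analysis that follows that text inherits the problem, and ordinary missing-data methods would not repair it.

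**Conclusion.** The concern holds in a conditional form. As listed, and under standard row deletion, the starting model and every step until previous birthweight leaves are fitted only to women who have one, and the nulliparous level of parity is lost in those fits. If the term is kept, the score cannot be computed for a first pregnancy.

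For an assumed 40-70% of the cohort with a previous birthweight, the fit rests on about 190-333 women and 38-67 events, below the plan's own 440 and 88. The size depends on that assumed share, on a 20% outcome rate in the subset, and, for the shrinkage column, on the back-solved 10 parameters. The direction does not: only a cohort at least 92.6% parous would meet the stated minimum. The same fault would reach the two secondary calculators if their candidate lists carry the term. It should be corrected before the first model is fitted; the Results section says that analysis has not yet been performed.

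**What to change.** State that women with no previous birth stay in every model, and recode the history variables so that they can:

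- Enter previous birthweight as a centred value multiplied by a parous indicator (0 for nulliparous women), beside the parity term. Keep the parity term whenever the product term is in the model.
- Give the previous LGA/SGA variable a no-previous-birth level. This level marks the same women as the nulliparous level of parity, so let one coefficient represent it and say which.
- Say which earlier birth supplies the value when a woman has had several.
- Treat a parous woman whose earlier birthweight is simply unknown as having ordinary missing data, distinct from a woman with no earlier birth.

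A simpler alternative is to drop the continuous term and use only the categorical growth history with its no-previous-birth level, at the cost of some information. The same coding should apply to the secondary calculators.

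The cost is a few lines in the analysis plan and no new participants. Earlier birthweight and gestation are already recorded at the first visit. If a previous-birthweight z-score is preferred, check first that everything the chart needs was collected: the earlier child's sex is not among the items the article lists.

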## Results

This project was funded by a National Health and Medical Research Council Investigator Grant awarded in November 2021 (CIA [name] 2022-2026; 2007957), and by a Translational Challenge Grant from the Ramsay Hospital Research Foundation awarded in April 2024 (CIA [name] 2024-2027; 2023/TCG/0038). The first participant was recruited on March 23, 2023. At the time of manuscript submission, 402 participants have been recruited. The projected timeline for recruitment is that the last participant will be recruited in June 2025. Therefore, it is anticipated that the last participant will have completed all study visits by June 2026. Data analysis has not yet been performed. Results are expected to be published in the first half of 2027.

## Discussion

### Why Predict Adverse Pregnancy Outcomes?

Uncontrolled maternal metabolic disease can profoundly impact both maternal and neonatal outcomes. Major congenital anomalies due to maternal metabolic disease are a common cause of neonatal death and long-term disability. For example, the risk of a major congenital anomaly such as congenital heart defect or spina bifida is 25% with suboptimally controlled diabetes (HbA_1c_ >10%) compared with 3% with well-controlled diabetes (HbA_1c_ <7%) [15,16]. Similarly, preterm birth can result in long-term neurodevelopmental issues and poor academic outcomes [17].

Even in children born at term, abnormal fetal growth can result in a long-term predisposition to metabolic disease. Around half of children born LGA (>90th centile for gestational age) or SGA (<10th centile for gestational age) [16] go on to develop metabolic syndrome (obesity, dysglycemia, and hypertension) by school age [2] with subsequent deterioration of metabolic disease in early adolescence [18]. This occurs due to a combination of factors including altered body composition at birth, altered appetite at birth, and atypical organ development including a lower endowment of cardiac myocytes, pancreatic beta cells, and nephrons [19].

For women, metabolic disease during pregnancy is an independent risk factor for later cardiovascular disease [20]. In the decade after preeclampsia, a meta-analysis including 200,000 women demonstrated a 4-fold increase in the relative risk of developing chronic hypertension and a 2-fold increase in the relative risk of ischemic heart disease and stroke [21]. For women who develop GDM, the lifetime risk of T2D is increased by 7-fold [22]. Lee et al [23] found that all-cause mortality was increased in women who were obese during pregnancy (BMI>30 kg/m^2^) versus normal BMI after adjustment for confounding factors (hazard Ratio 1.35, 95% CI 1.02-1.77). Pregnancy loss due to late first-trimester miscarriage or stillbirth is also associated with increased cardiovascular disease in the mother, likely because pregnancy unmasks an underlying endothelial dysfunction [15].

### Why Existing Prediction Models Are Inadequate

There are very few studies that have aimed to predict adverse pregnancy outcomes based on the maternal phenotype, and most of these have used maternal characteristics in combination with obstetric tests such as biomarkers in blood or ultrasound [24-27]. To the investigator’s knowledge, there has only been one study that has used maternal prepregnancy characteristics to predict the risk of poor pregnancy outcomes [28].

The Generation R study group used easily obtainable maternal preconception characteristics including age, ethnicity, parity, BMI, and smoking status to model the risk of offspring born LGA/SGA. Basic models demonstrated an AUC of 0.63 (95% CI 0.61 to 0.65) and 0.64 (95% CI 0.62 to 0.66) for preterm birth/SGA and LGA, respectively. Interestingly, more complex models involving sociodemographic and dietary details only led to small improvements in the model [28].

However, the Generation R study was a population-based prospective cohort study that aimed to identify early and genetic causes and casual pathways leading to abnormal growth and development of the offspring [29]. Risk prediction modeling in this study focused on all potential causes of LGA and SGA in a whole population cohort. This study did not specifically focus on LGA/SGA in the context of metabolic disease, nor did it consider the metabolic outcomes of the mother. Women with metabolic disease are known to be at higher risk of adverse pregnancy outcomes than the general population [30]. This cohort requires information about the risk of poor pregnancy outcomes both for themselves and their offspring.

Within an established pregnancy, Frick et al [31] found that LGA offspring (>95th centile) could be predicted based on increasing maternal BMI, diabetes status, and the presence of chronic hypertension. However, this prediction was less accurate in non-Caucasian women, in smokers, and in nulliparous women. In parous women, LGA offspring were predicted based on the birth-weight Z-score of previous offspring, a prior history of GDM, and a decrease with interpregnancy interval. This study then refined the prediction model using early fetal ultrasonography [31].

A population-based study from Ontario Canada (n=634,290) found that it was possible to predict and prevent severe maternal morbidity with moderate discrimination. Those women who had poor short-term pregnancy outcomes were older, had more medical comorbidities, and conceived using assisted reproductive technologies [32]. Similarly, Akinci et al [33] reported that in a small cohort (n=164), prepregnancy obesity, greater gestational weight gain, and a fasting glucose level (>5.5 mmol/L) on the 75-g OGTT predicted the development of metabolic syndrome in postpartum women with moderate to high discrimination.

